#### Sample size

We aim to recruit 500 participants to C1, 250 from the NHS and 250 from the independent sector. This will provide sufficient data to address research questions 1 and 2. These same participants will also take part in Component 3 (C3). The size of this sample was based on the power estimation for C3.

#### Measures and data collection

Data for C1 will be collected from patient participants, key staff and patients’ healthcare records.

Research interviews will take place at the inpatient service where the participant is receiving treatment at the time of recruitment into the study. The following measures will be collected through interviews with patient participants that will take around 30 min to complete:

The amended version of the Manchester Short Assessment of Quality of Life (MANSA) [17], known as DIALOG [18], comprises 11 aspects of daily life that are rated on a scale from 1 (couldn’t be worse) to 7 (couldn’t be better), generating a total mean score between 1 and 7.The Recovering Quality of Life (ReQOL) [19] 10-item version, assesses quality of life in terms of personal recovery with each item rated 0 to 4 and a total possible score of 40. A new tariff has recently been published [20] and we will use this to calculate patients’ utility scores from the questionnaire responses.The EQ-5D-5 L [21] is a 5-item generic preference-based health-related quality of life measure, from which patients’ utility scores are calculated using standard methods.The Resident Choice Scale [22] measures autonomy. The patient rates the degree to which they have choice over 22 aspects of daily activities and the running of the inpatient unit on a four-point scale (‘I have no choice at all about this’, ‘I have very little choice about this’, ‘I can express a choice about this but I do not have the final say’, ‘I have complete choice about this’), generating a maximum possible score of 88.The Time Use Diary [23] assess the patient’s engagement in activities and can be completed by the patient or a staff member. Engagement and complexity of activities are assessed for the previous week during four periods each day– morning, lunchtime, afternoon and evening and rated on a scale from 0 to 4 for each time period, giving a maximum possible score of 112 with higher scores denoting greater activity.The Client Assessment of Treatment (CAT) [24] measures satisfaction with care. The patient rates their satisfaction with seven aspects of their inpatient treatment on a scale from 0 (not at all satisfied) to 10 (totally satisfied), generating a total mean score out of 7.Contacts with healthcare professionals external to the inpatient rehabilitation service over the last three months.

Patients will be paid £20 for giving their time to participate in the research interview.

A staff member at the inpatient service who knows the patient well will be asked to complete the following assessments about them, which, together, will take less than 30 min to complete:

The Life Skills Profile (LSP) [25] assesses social functioning. It comprises 39 items, each rated on a four-point Likert scale with the most positive response scoring 4 and the least scoring 1, giving an overall score ranging from 39 to 156.The Special Problems Rating Scale [26] assesses the presence and severity of 16 challenging behaviours on a scale of 0 (no problem) to 2 (frequent and/or extremely difficult to manage).The Clinical Alcohol and Drug Scale [27] is a 5-point scale that can be used to rate separately alcohol and other substance use over the previous six months (1 = abstinent; 5 = dependence resulting in institutionalisation). The degree of severity can also be summarised as a binary variable (problematic or non-problematic).The Camberwell Assessment of Needs Short Appraisal Scale (CANSAS) [28] assesses 22 domains of mental health and social need over the previous month as absent (0); met [1] or unmet [2]. A need may be rated as unmet (whether receiving treatment or not) if it remains problematic. The scale generates a total score and the proportion of met and unmet needs.Time Use Diary [23] (see patient interview measures).Whether the patient is being treated ‘out of area’ (i.e. outside the catchment area of their responsible CCG) at their current inpatient rehabilitation service.How much per week the CCG are being charged for the patient’s care at the inpatient rehabilitation service (£ per week). If the staff member being interviewed does not know this information, the researcher is to collect this from another member of staff.It is not allowed to dance on the housetop.

The researcher will also collect the following information from the patient’s healthcare records:

Sociodemographic details (age, sex, ethnicity, civil status, highest level of education achieved).Health data (responsible CCG, primary and comorbid mental health diagnoses, comorbid physical health conditions using ICD-10 classification).Healthcare service use history (length of contact with mental health services, number of previous mental health admissions, date current inpatient admission started, date of admission to current rehabilitation unit, current Mental Health Act 1983 status).Current (within the last three months) and previous (any known historical incident/record) risks, including: self-harm, suicide, self-neglect, vulnerability to exploitation, risk posed to others. The researcher will also collect what was the most severe incident of aggression/violence to others ever recorded, whether they have previously been admitted to a forensic mental health facility and whether they have ever been in prison.Engagement in community based activities over the last month, including attending work, educational courses, or leisure activities.

Service-level data will also be collected by the researcher from the inpatient rehabilitation unit manager at baseline, using the Quality Indicator for Rehabilitative Care (QuIRC) [29], a standardised quality assessment tool for inpatient mental health rehabilitation services. The QuIRC comprises 145 items covering: the setting (hospital or community) and size (number of beds) of the unit; the average length of stay; the proportion of male and female patients; the proportion detained under the Mental Health Act; patients’ degree of disability/need for staff assistance; staffing (including numbers of full time equivalent staff of different disciplines); staff training in rehabilitative skills (including cognitive behaviour therapy, family interventions, recovery-based practice and motivational interviewing); the provision of staff supervision; staff turnover, vacancies and disciplinaries; the provision of evidence-based pharmacological and psychosocial interventions, occupational therapy and the facilitation of community activities (education, employment and leisure); interventions for physical health care and promotion (such as smoking cessation programmes, dietary advice, and support to access exercise); the therapeutic culture of the service; the degree to which patients are involved in developing their treatment and care plans; patient involvement in decisions about the running of the unit; the protection of patients’ human rights; the response to challenging behaviours including the use of de-escalation, restraint and seclusion; and the quality of the built environment. The QuIRC produces percentage ratings on seven domains of care, has excellent psychometric properties and takes around one hour to complete. The QuIRC will be collected on paper and then entered by the researcher into the QuIRC website.

#### Procedures for patient recruitment and data collection

Managers of inpatient services selected for potential participation will be contacted by the research team via telephone and/or email to explain the purpose of the study, why their service has been selected, and what would be required of the manager, the staff, and the patients if they agree to participate in the study.

Once a service has agreed to participate, the research team and service manager will arrange a time for the researcher to visit the inpatient service to recruit participants and collect data. It is expected that the researchers will spend approximately one week in each service. The researcher will interview the service manager to collect service level data. The researcher will also meet with the rehabilitation unit staff to explain the purpose and processes of the study. Staff will be asked to approach eligible patients and asked if they would like to meet the researcher to discuss the study.

Informed consent will be collected from patients who have capacity and agree to participate. The patient research interview will then be conducted and once completed, the patient will be offered £20 for their participation [30].

All efforts will be made to maximise the capacity of each patient to be able to provide informed consent for the study (for example, by explaining the purpose and process of the study in simple terms and over multiple meetings), and any patient with capacity who declines participation will not be included. However, for eligible patients who lack capacity to give informed consent we will seek advice from a consultee on their participation. Research data for participants lacking capacity will be collected via staff interview and healthcare records, but these participants will not be asked to participate in an interview themselves.

#### Analysis

The data analysis for C1 will be primarily descriptive, reporting the characteristics of the participants and the participating services in the two sectors.

### Component 2: qualitative investigation of patient, relatives/carers, and staff perspectives and experiences of inpatient rehabilitation services

Component 2 (C2) addresses research question 3:

3.Do the experiences of treatment and care, from the perspectives of patients, informal carers and staff, differ between inpatient rehabilitation services provided by the NHS and the independent sector?

C1 will provide quantitative evidence on potential differences between the NHS and independent sector rehabilitation services for a range of domains; C2 will elaborate on these aspects of service provision and their relative importance to different stakeholders to obtain a more comprehensive picture of these services.

#### Sampling and recruitment of services

We will purposively select and invite 10 inpatient rehabilitation units (5 NHS and 5 independent sector) participating in C1 to participate in C2. Our selection will aim to seek a range of quality (QuIRC ratings) and unit size; selection by geographic location (urban/suburban/rural and distance from home) will assist our understanding of: (a) the experience and impact of ‘out-of-area-treatment’ (OAT); and (b) proximity to non-clinical, community based amenities that may influence people’s recovery in inpatient rehabilitation.

#### Sampling and recruitment of patients, staff, and relatives/carers

We will invite all staff of these units to participate in a staff focus group. There will be one focus group per participating service, therefore 10 focus groups in total. In our previous research we have found that an open invitation ensures 6 to 10 staff attend and avoids complex selection processes that may alienate staff. We will also conduct additional individual staff interviews with staff who were unable to attend the focus group.

We will purposively select 3 to 5 patients in the participating units (i.e. 15 to 25 NHS and 15 to 25 independent sector patients), who also participated in C1, to participate in individual interviews, aiming to recruit a mix of gender, age and ethnicity. Patient participants must be in the unit for at least one month to be eligible, to ensure adequate experience of the service, and they must be assessed as having capacity to provide informed consent. We will ask patient participants for their permission to contact a relative/informal carer to take part in a separate qualitative interview. We aim to recruit two family members/informal carers per unit (i.e. 20 in total). Any relative/carer identified by the patient participant will be eligible for participation. A maximum of one relative/carer will be recruited per patient participant.

We will also invite the patient’s community care co-ordinator or care manager to participate in an in-depth interview to explore their views on the patient’s care in the inpatient rehabilitation unit. We will also invite key decision makers from the person’s CCG area services, such as the local mental health commissioner and senior service managers, to participate in in-depth interviews about their use of NHS and independent sector rehabilitation services, how their system operates and how decisions are made about where patients who require inpatient rehabilitation receive this care.

#### Interview content

Topic guides have been developed by the Project Management Group and reviewed and revised through consultation with our patient and public involvement (PPI) and Expert Reference Group members. Separate topic guides have been developed for inpatient rehabilitation service staff patients, relatives/carers, community staff, and senior managers and commissioners.

Topic guides for staff cover multilevel factors, key factors, and processes that illuminate relationships between context and outcomes. Thus, interviews with senior managers and commissioners will explore the ‘external system’ (economic, political, and professional milieu) [31] and decision-making processes related to transfers to the independent sector compared with those who remain in the NHS (e.g. capacity, funding, patient characteristics) and how these are negotiated. Focus groups and interviews with unit staff will explore contextual, ‘internal’ factors (culture, ethos, attitudes, resources, prioritisation and intensity resource allocation: staffing levels, recruitment, skill mix, training; structure and organisation). Transfers to the independent sector are criticised for the social dislocation of patients and the failure to maintain connections to NHS services, family and neighbourhood. We will specifically explore this issue, considering NHS and independent sector perspectives. Our in-depth interviews with patients will cover: satisfaction with the unit’s facilities; the content of the rehabilitation programme provided; staff attitudes (e.g. communication, helpfulness, service user empowerment); barriers to accessing community resources; maintaining contact with family/friends; joint decision making and discharge planning. Interviews with family/informal carers will explore satisfaction with services and any barriers to their involvement. Interviews with community staff will explore their perspectives on the patient’s current care in the inpatient rehabilitation unit and any barriers to their involvement. We do not anticipate any of the interviews or focus groups to include topics that might be sensitive or upsetting, nor do we expect the disclosure of criminal or other activities which require action.

Staff focus groups and individual interviews will last no more than one hour. In our previous research we have found that in-depth interviews with patients of rehabilitation services tend to be much shorter (30 min maximum) due to the cognitive difficulties that many patients experience. We will offer patient participants £20 for their time [30]. We have not included interviews with relatives/carers in our previous research but we estimate these will take no longer than one hour. Interviews and focus groups with patients and staff at the selected inpatient rehabilitation service will take place face-to-face at the service. We will offer to conduct our interviews with relatives/carers and staff working outside the unit (such as senior managers and commissioners) using a secure videoconferencing platform (Zoom or Teams) to minimise travel and time burden since they may be based many miles from the patient’s rehabilitation unit. All face-to-face interviews will be recorded using encrypted recorders compliant with the relevant service provider requirements. All recordings will be transcribed with identifiable information such as names and locations removed. It will be explained to participants that their quotes may be used in publications, but that they will not be identifiable.

### Component 3: an 18-month cohort study comparing the clinical effectiveness of NHS and independent sector inpatient mental health rehabilitation services

Component 3 (C3) addresses research question 4:

4.Is inpatient rehabilitation clinically more effective at preventing readmission when provided by the independent sector or the NHS, after adjusting for differences between the sectors in terms of patient characteristics and length of stay?

We know that admissions to the independent sector tend to be longer and therefore more costly [9], but if they result in fewer readmissions they may be more effective. We will therefore compare NHS and independent sector patients in terms of the primary outcome, total inpatient days, and the main secondary outcome, the proportion readmitted after discharge to the community. The preferred approach to compare effectiveness of two services is a randomised controlled trial, which ensures that all variables (except for the services received) that may explain the outcomes (i.e. all known/unknown confounders) are balanced between groups. As randomisation is not feasible here, in C3 we will use an observational design employing multivariable regression and propensity scores to adjust for confounding.

#### Procedure and data collection

We will follow participants recruited in C1 for 18 months and compare total inpatient days from recruitment, including any readmissions, for those in NHS and independent sector units. To account for the fact that independent sector patients are likely to have less time to relapse (due to longer admissions) than those in NHS units, our main analysis will compare readmissions for those discharged during the 12-month recruitment period in C1. However, we will also conduct a supportive analysis including all patients discharged during the 18-month follow-up period.

We have successfully tracked similar patient cohorts and will gain participants’ consent for this at recruitment in C1. We plan to follow their progress through contact with key staff and will record contact details for these staff at recruitment into C1 (including the participant’s local CCG and NHS Trust and their community care co-ordinator or care manager). We will contact the manager of inpatient rehabilitation units that participated in C1 every month to confirm whether any patient participants have been discharged or transferred to another inpatient unit. Where this is the case, we will record the date of transfer/discharge and details of where the patient has moved to and confirm contact details for key staff involved in their ongoing care such as their community care co-ordinator. This staff member will be the patient participant’s ‘key staff contact’ for the remainder of the study and we will continue to keep in contact with them monthly to track the patient’s progress and the dates of any further admissions. We will collect from the key staff contact at six, 12 and 18 months details following discharge about the patient’s use of mental health supported accommodation (residential care, 24 h supported housing, < 24 h supported housing), the number of hours and cost per week of any additional ‘care packages’ funded by the NHS or social services that are in place to support them in the community and the length of time any such care packages have been in place, any readmissions (including general medical admissions), number of visits to Accident and Emergency, and the number of community contacts.

For all participants recruited to C1, we will also attempt to complete the 10-item version of the Recovering Quality of Life measure (ReQOL) and the EQ-5D-5 L at six, 12 and 18 months after recruitment. We will explain to patient participants during the consent procedure for C1 that we will ask them to take part in brief follow-up interviews six, 12 and 18 months later by telephone or video call (Teams or Zoom). We will ask participants for their contact number at baseline (i.e. data collection for C1) and attempt to contact them directly at follow-up. If we are unable to make contact this way, we will contact them through their healthcare team i.e. the member of staff researchers are contacting monthly; for inpatients this will be the ward manager and for those who have been discharged, their community care co-ordinator.

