**Methods:**

ACER comprises a:1) detailed survey of NHS and independent sector inpatient mental health rehabilitation services across England; 2) qualitative investigation of patient, family, staff and commissioners’ experiences of the two sectors; 3) cohort study comparing clinical outcomes in the two sectors over 18 months; 4) comprehensive national comparison of inpatient service use in the two sectors, using instrumental variable analysis of routinely collected healthcare data over 18 months; 5) health economic evaluation of the relative cost-effectiveness of the two sectors. In Components 3 and 4, our primary outcome is ‘successful rehabilitation’ defined as a) being discharged from the inpatient rehabilitation unit without readmission and b) inpatient service use over the 18 months.

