#### Analysis

We will conduct two statistical analyses using the information collected from C1 and C3:

i.Multivariable regression

We will conduct linear regression using total inpatient days (since recruitment to C1) as our primary outcome and logistic regression using proportion of patients readmitted as our main secondary outcome, allowing for clustering within inpatient rehabilitation units. Service sector (independent or NHS) will be included in the model as the main explanatory variable. We shall adjust for relevant sociodemographic and clinical confounding variables, including inpatient days up to recruitment (gathered in C1), which may account for differences in outcomes between the two service types. We will use Directed Acyclic Graphs (DAGs) to ensure a logical and consistent approach to identifying potential confounders [36]. Suitable transformations will be used if assumptions of normality for linear regression are not satisfied. In addition, we will conduct exploratory analysis to investigate the relationship between the length of the inpatient rehabilitation admission (i.e. ‘dose’ of rehabilitation assessed in inpatient days), readmission and the service sector (independent or NHS), through a mediation analysis. Bias due to missing data in the explanatory variables (gathered in C1) will be investigated and we will use multiple imputation based on chained equations to impute missing values for these variables as appropriate.

ii.Multivariable regression with propensity score

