Anonymous patient identifier (linked to NHS number with key held by NHSE and not available to the research team).The CCG funding the inpatient rehabilitation admission.Baseline (i.e. census date: 1st February 2021) rehabilitation admission provider: NHS/Independent.Start date of the baseline rehabilitation admission.Start date of the baseline rehabilitation admission ‘spell’ (most inpatient rehabilitation patients are transferred from another inpatient ward; the ‘spell’ refers to the period when the patient was first admitted from the community to the point they are discharged to the community, including any transfers between inpatient wards).Gender at baseline.Age at baseline.Ethnicity.Rating of each Health of National Outcome Scale (HoNOS) item (12 in total) for HoNOS assessments recorded between the date 12 months before the census date (i.e. 1st February 2020) and the 18-month end date (i.e. 1st August 2022).HoNOS assessment dates.Inpatient service use during the cohort period (i.e. baseline date to 18-month end date).Discharged from the baseline inpatient rehabilitation admission: Yes/No.Date of discharge from the baseline rehabilitation service.Start and end date of any inpatient admission following discharge from the baseline rehabilitation admission, and the 18-month end date.

The 1st February 2021 was set as the census date in order that the 18 month study period (a) minimised the amount of time when Trusts were still affected by the COVID-19 pandemic and (b) avoided the impact of the cyber-attack of mid-August 2022 which affected several NHS Trusts. Trusts affected by the cyber-attack were unable to provide any data, including inpatient service use data, to NHS England for several months following the attack.

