#### Analysis

Using appropriate regression models, we will estimate associations (1) between the IV and type of service received (NHS or independent sector) and (2) between the IV and successful rehabilitation. We will then investigate imbalance in key confounding factors (e.g. age, gender, latest HoNOS score) for the IV. The main analysis is a regression model using only the IV value as the predictor of outcome (total bed days over the 18 months follow-up). Then as part of the sensitivity analysis we shall rerun the regression analysis including key confounding variables that are potentially unbalanced in the regression model, in addition to the IV. As part of sensitivity analyses, different thresholds will be explored to construct the IV, based on the probability of CCGs outsourcing inpatient rehabilitation to the independent sector. Bias due to missing data will be investigated if applicable and sensitivity analyses under plausible missing data assumptions performed. Multiple imputation for missing data will be used if appropriate.

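### The Component 4 extract lists neither date of death nor discharge destination, so a death cannot be told apart from a discharge home without readmission

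*Protocol article*

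**What the plan says.** The Abstract defines successful rehabilitation for Components 3 and 4 as "being discharged from the inpatient rehabilitation unit without readmission and b) inpatient service use over the 18 months". Neither part carries a condition that the patient is alive.

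In Component 4 the main analysis uses the instrument alone as "predictor of outcome (total bed days over the 18 months follow-up". The data come from NHS England as an enumerated set of variables. For leaving the baseline unit and what follows, the list has "Discharged from the baseline inpatient rehabilitation admission: Yes/No", the date of that discharge, and start and end dates of any later admissions up to the 18-month end date. It has no date of death and no discharge destination.

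Component 3 is described differently. It will "compare total inpatient days from recruitment, including any readmissions", and its primary analysis is "linear regression using total inpatient days (since recruitment to C1) as our primary outcome". Its main secondary outcome is "the proportion readmitted after discharge to the community". Unit managers are contacted monthly, and when a patient leaves, "we will record the date of transfer/discharge and details of where the patient has moved to". A key staff contact is then followed monthly.

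The protocol article does not mention death as an outcome, a censoring or competing event, or a data item.

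**The concern.** Fewer days and no readmission are the good results. A patient who dies accrues no further days and cannot be readmitted, so death moves both measures in the favourable direction. Where deaths can be seen, the analyst can decide how to treat them. In Component 4 they cannot be seen. A patient who died in the unit, one who died soon after going home, and one who went home and stayed well could all show the same record: discharged, with a date and no later admission.

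At stake is the sector comparison in the national dataset. If mortality differed between the sectors, part of any difference in bed days or in discharge without readmission would reflect deaths, and nobody could check how much. The Background describes physical comorbidity, including diabetes and cardiovascular and pulmonary disease, so some deaths over 18 months are foreseeable.

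**Working it through.** **The plan's own figures.** For 0.38 SD, 90% power and two-sided 5%, the exact t test needs 147 per group, 294 in all. The VIF is 1/(1 − 0.16) = 1.19, giving 350. The Component 3 design effect is 1 + 7 × 0.06 = 1.42, giving 350 × 1.42 = 497. For Component 4, 1 + 13 × 0.06 = 1.78 and 350 × 1.78 = 623; the expected sample is 4,400 × 0.85 = 3,740. All reproduce and none is in dispute. The target difference is 0.38 × 113 = 42.9 days.

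**Shift in bed days.** Shift = (sector difference in 18-month mortality) × (mean inpatient days cut off per death).

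The protocol gives neither factor, so both are assumptions. Follow-up is 18 × 30.44 = 548 days. A death at mid-follow-up leaves 274 days. If the patient would have spent half to all of them in hospital, 137 to 274 days are cut off.

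| Mortality difference | Shift in days | Share of 42.9 days |
|---|---|---|
| 1 point | 1.4 to 2.7 | 3% to 6% |
| 2 points | 2.7 to 5.5 | 6% to 13% |
| 3 points | 4.1 to 8.2 | 10% to 19% |
| 5 points | 6.9 to 13.7 | 16% to 32% |

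This range is not a ceiling: at 400 days cut off per death, one point gives 0.01 × 400 = 4.0 days. To produce the whole target, death alone would need a mortality gap of 42.9/274 = 16 points to 42.9/137 = 31 points.

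**Against the precision.** With the plan's SD and inflation factors:

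- Component 4, equal split assumed, ordinary regression: SE = 113 × √(4/3,740 × 1.19 × 1.78) = 5.4 days. An instrumental variable estimate would have a larger SE.
- Component 3, 250 per sector: SE = 113 × √(2/250 × 1.19 × 1.42) = 13.1 days.

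A 2-point gap at 274 days per death (5.5 days) is about one Component 4 SE, but only 5.5/13.1 = 0.4 of a Component 3 SE.

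**Readmission, for illustration.** Take the plan's 33% for NHS patients and suppose that 3% of discharged patients die before any readmission and would otherwise have been readmitted at the same rate. Counting deaths as not readmitted gives 0.33 × 0.97 = 32.0%. Counting death as failure gives 32.0% + 3% = 35.0%.

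**What the listed fields can recover.** A transfer to another ward can be partly inferred when a later admission starts as the earlier one ends. A death cannot be inferred from any listed field.

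**The case against.** The strongest objection is that the case rests on silence. A reader might infer that the plan scores death as a success; no passage says so. This is a journal article, and how deaths are analysed is commonly left to the full protocol or SAP. That stands for the method of analysis. It does not answer the Component 4 field list, because an analysis plan cannot use a variable that was not requested.

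A reader might extend the point equally to Component 3. The document does not support that. Its readmission outcome is conditional on discharge to the community, which an in-hospital death is not, and monthly tracking with a record of where the patient went would very likely reveal deaths. What remains there, the day count and deaths after discharge, can be handled with data the team will hold.

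Total inpatient days is also a legitimate resource-use measure. The sample size section justifies the target by bed-day cost, and for cost the days used up to death are the right count. That stands, and is why total bed days should remain the main outcome.

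Three further inferences go too far:

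- Applying an assumed 2% to 4% mortality to 3,740 people would give about 75 to 150 wrongly counted as successes. That does not describe the main analysis, which is of bed days, and it supposes that nobody who died had been readmitted first.
- The direction of any error between sectors is unknown, because the protocol gives no reason to expect higher mortality in either. Similar mortality would largely cancel.
- The gap is not beyond repair. The request is described as still to be made, and NHS England holds the key to the identifier, so a supplement is not ruled out.

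Finally, the protocol does not say how an in-unit death appears in the discharge field. If it were coded as not discharged, the patient could seem to occupy a bed to the end date, and the error would run the other way. This qualifies the direction for in-unit deaths but strengthens the case for the field, since neither coding could be detected without it.

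**Conclusion.** The point holds for Component 4. As listed, the extract cannot separate death from discharge home without readmission, and both total bed days and "being discharged from the inpatient rehabilitation unit without readmission" would favour a sector with higher mortality. For in-unit deaths this assumes that death closes the admission record.

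The size is assumption-based: about 1.4 to 2.7 days per percentage point of mortality difference, with 137 to 274 inpatient days cut off per death. The bias is modest unless mortality differs between sectors, and death alone is an implausible source of a full 42.9-day difference. In the instrumental variable analysis, the mortality difference that matters is the one that follows the instrument. Without the field it cannot be examined there either. In Component 3 the matter is one of recording and analysis, not of missing data. This is a cheap improvement, not a flaw that undermines the design.

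**What to change.** - **Component 4 data request:** add date of death and discharge destination.
- **Discharge and readmission outcome:** state that death does not count as successful rehabilitation.
- **Bed days:** keep total bed days as the main resource-use outcome. Add one sensitivity analysis that accounts for death, for example days alive and out of hospital, or bed days per day alive.
- **Component 3:** record deaths, with dates, in the monthly tracking and use them in the same sensitivity analysis.

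The cost is one or two extra fields in the data-sharing request, one tracking item and one extra analysis. The change is easiest before the extract is requested; afterwards it would need a supplementary request.
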